#### Secondary outcomes

The Beck Depression Inventory-II (BDI) is a common self-rating assessing the severity of depressive symptoms. The instrument features good characteristics for internal consistency, test-retest reliability and validity [46]. The subjective quality of life will be measured by the World Health Organization Quality of Life–abbreviated (WHOQOL-BREF), an interculturally valid, multidimensional questionnaire with good to excellent psychometric properties [47]. The 18-item version of the Brief Symptom Inventory (BSI) is a short, reliable and valid self-assessment instrument for general psychopathology [48]. The 20-item-version of the Kentucky Inventory of Mindfulness Skills (KIMS) will be used to measure dispositional mindfulness [49]. The instrument has good discriminant and convergent validity and is sensitive to changes over the course of MBCT [50]. The Obsessive-Compulsive Inventory Revised (OCI-R) is a self-rating scale assessing the major symptoms of OCD on six dimensions (see [51] for the German version). The Obsessive Beliefs Questionnaire (OBQ) is a multidimensional instrument assessing dysfunctional metacognitive beliefs in the context of OCD. The questionnaire has shown a satisfactory reliability and validity (see [52] for the German version) and is sensitive to therapeutic changes [53]. In addition to the OBQ, the short form of the Metacognitions Questionnaire (MCQ-30) will be used. The MCQ-30 is a brief questionnaire with good indices for reliability and validity [54]. The instrument’s sensitivity to therapeutic changes has been shown for the long version [55]. The Distress Tolerance Scale (DTS) [56] measures the capacity to experience and withstand negative psychological states. As a German version of the instrument is not yet available, the DTS was translated by our workgroup. Moreover, the self- compassion scale (SCS) measures the capability of cultivating self-kindness, common humanity and mindfulness even when things go bad instead of self-judgment, feelings of isolation and over-identification (see [57] for the German version).

Diagnoses will be made by trained staff using the Mini International Neuropsychiatric Interview (M.I.N.I.). The M.I.N.I. is a structured diagnostic interview for DSM-IV and ICD-10 psychiatric disorders [58]. The Suicidal Behaviors Questionnaire-Revised (SBQ-R) [59] and the Test of Word Power (WST), which is a short, valid instrument assessing general intelligence [60] will be administered at baseline. Besides, the Autism Spectrum Quotient (AQ) [61] will be applied at baseline for assessment of autistic traits. In addition, sociodemographic variables and a questionnaire concerning satisfaction with the result of randomization and motivation, constructed by the workgroup will be administered. The medication status will be enquired and documented at all times of assessment. Subjective treatment satisfaction will be assessed after the program by the Treatment Satisfaction Questionnaire (ZUF-8). Moreover, a questionnaire called “Side-Effects of Psychotherapy” scale (SEPS), based on items of the Inventory of Negative Effects of Psychotherapy (INEP) [62], a scale assessing negative effects of psychotherapy in different areas of life, as well as items constructed by the workgroup assessing negative outcomes of the intervention, will be administered post treatment and follow-up. At both follow-ups, participants will be asked about significant life events within the follow-up period.

In addition, an approach-avoidance-task (AAT) [39], a computerized neuropsychological paradigm, will be applied by comparing response times for OCD-related (checking and contamination) and neutral words and pictures, before and after treatment. In this task, patients are instructed to respond to each stimulus presented on the computer screen by pushing or pulling a joystick. When participants push the joystick away from themselves, the picture on the screen shrinks, creating the visual impression that the stimulus moves away. When they pull the joystick, the picture grows until it fills the screen, creating the impression of an approaching stimulus. Response times for pulling and pushing stimuli away can be compared in order to assess automatic avoidance tendencies. A similar version of the AAT used in the present study has already been applied in another study on OCD patients [63].

Moreover, in order to investigate the participants’ experiences in situ as an additional outcome measure of MBCT and to gain further insight into the relationship of emotions and OCD symptoms, the Experience Sampling Method (ESM) [40] will be applied to a subset of the study sample before and after treatment. Participants will be asked to record their OC symptoms, the distress caused by symptoms, affective states and acceptance of unpleasant affective states respectively on an electronic device 6 times a day on 6 consecutive days before and after the group interventions. The prompts to fill out a form will be given at random time-points between 8 am and 22 pm by the web-based experience sampling software *movisensXS* (movisens GmbH, Karlsruhe). Partici\pants who decide to take part in this additional paradigm will receive 50€ for compliance rates of at least 80% and a short summary of their mood profile and symptoms before and after treatment.

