Further exploratory research questions include the effects of MBCT on secondary outcome measures such as comorbid depressive symptoms (as measured by the Beck Depression Inventory), Quality of Life (World Health Organization Quality of Life BREF), the general psychopathology (Brief Symptom Inventory), the tendency to be mindful in everyday life (Kentucky Inventory of Mindfulness Skills), distress tolerance (Distress Tolerance Scale), self-compassion (Self-Compassion Scale) and dysfunctional beliefs and attitudes (Obsessive Beliefs Questionnaire, Metacognitions Questionnaire). The relationship between mindfulness, distress tolerance and dysfunctional attitudes on the one hand and changes of clinical symptoms on the other hand will be addressed in exploratory analyses. Possible negative effects of the MBCT and OCD-EP treatment will also be explored. Additionally the change in avoidance tendencies will be assessed using an approach avoidance task (AAT) [39] measuring avoidance tendencies to contamination and checking related words and pictures. A subgroup of the sample will also take part in an additional experience-sampling task to examine changes in positive and negative affect, distress caused by OC symptoms, insight into the unreasonableness of obsessions as well as acceptance of unpleasant feelings before and after treatment. The experience sampling method (ESM) [40] is characterised by the repeated collection of real-time data on participants’ momentary inner states in their typical environments, thereby aiming to minimize memory biases and ensuring ecological validity [41].

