### Setting

Overall, eight MBCT- and eight OCD-EP-groups will be conducted (four MBCT- und four OCD-EP-groups at each site). The baseline assessments (T0) and post-assessments (T1) will be performed directly before respectively after the interventions. The first follow-up (T2) will be six months and the second (T3) will be 12 months after the end of the intervention.

The two participating centers will be the University Medical Center Freiburg and the University Medical Center Hamburg-Eppendorf. Both centers will recruit equal proportions of participants. Potential distortions due to the bicentric approach will be controlled by a stratification and by homogeneous study conditions (same room equipment, same training of the therapists, same measures, etc.).

The bicentric study was approved by the ethics commission of Freiburg University Medical Center. In accordance with the Declaration of Helsinki, all participants will be informed in detail about the design and purpose of the study. Each participant will be required to sign a written consent form and will have the freedom to withdraw consent and quit the study at any point in time. Data will be documented anonymously in a case report file (CRF), which will be stored at the University Medical Center Freiburg for 10 years. All necessary personal data will be kept confidential. All sessions will be videotaped, supervised and checked for adherence. Supervision will be provided by [name], University of Esslingen.

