### Sample size

A power analysis was performed with the program “G*Power” [42]. Based on the pilot data, on results of comparable studies [24,43] and on theoretical considerations, we assume a between-group effect size of *d* = 0.5 favoring MBCT. Assuming an a priori test power of 0.8, a total sample size of *n* = 128 (*n* = 64 per intervention) will be sufficient to detect this effect by an *F*-test in an ANOVA at *p* < .05 level of significance for a group × timepoint interaction. We assume a dropout rate of approx. 15% and thus target a total sample size of *n* = 148.

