### Statistical analyses

Between-group comparisons at baseline will be performed using analyses of variance for the continuous variables and Fisher’s exact test for the categorical variables. Means and standard deviations will be calculated for descriptive purposes. The main analyses will be computed using analyses of covariance in view of statistical studies suggesting that controlling for the baseline score is superior to simple pre-post comparisons and usually leads to an increase in power. An advantage of this type of analysis over mixed models is that it accounts for baseline differences and regression to the mean (i.e. higher scores usually yield greater improvement). The rates of patients achieving response and/or remission and the relapse rates in both groups will be compared using Fisher’s exact test. The time to relapse will be estimated using Kaplan-Maier survival analyses. Survival curves will be compared using a log-rank-test. A cox-regression will be performed to analyze variables influencing the time to relapse. In order to prevent distortions, the intent-to-treat principle will be used. Multiple imputation will be adopted to estimate post-treatment and follow-up scores for non-completers (i.e. no data available at reassessment). The multiple imputation principle is considered superior to the last observation carried forward method (LOCF) [64]. When using the LOCF, follow-up data can be difficult to interpret [10].

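### The negative-effects questionnaire is scheduled only at reassessment, so it misses negative effects in patients who quit before T1 and are never reassessed

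*Protocol article*

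**What the plan says.** - **What is measured and when.** The Secondary outcomes section describes the SEPS, built on items of an existing inventory of negative effects, "as well as items constructed by the workgroup assessing negative outcomes of the intervention, will be administered post treatment and follow-up".
- **Visit times.** Under Setting, "The baseline assessments (T0) and post-assessments (T1) will be performed directly before respectively after the interventions". In addition, "The first follow-up (T2) will be six months and the second (T3) will be 12 months after the end of the intervention".
- **Purpose.** The Study design section makes harm an exploratory question for both arms: "Possible negative effects of the MBCT and OCD-EP treatment will also be explored".
- **Leaving.** Under Setting, each participant "will have the freedom to withdraw consent and quit the study at any point in time".
- **Expected loss.** Under Sample size, "We assume a dropout rate of approx. 15% and thus target a total sample size of" 148.
- **Missing data.** Under Statistical analyses, "In order to prevent distortions, the intent-to-treat principle will be used" and "Multiple imputation will be adopted to estimate post-treatment and follow-up scores for non-completers (i.e. no data available at reassessment"). The section does not mention the SEPS or negative effects.

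**The concern.** Under the stated schedule, the first chance to report a negative effect on this scale comes after the eight-week programme. A patient who withdraws from the study during those weeks and does not come back for T1, T2 or T3 never completes it. A negative effect may itself be a reason to withdraw, so the missing reports may not resemble the ones collected.

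The scale is also harder to repair than the symptom measures. A patient lost before T1 still has a baseline Y-BOCS to inform imputation, but has no SEPS value at any time.

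What is at stake is the trial's own comparison of negative effects between MBCT and OCD-EP. If one arm loses more patients through negative effects than the other, the difference seen among attenders is too small or absent.

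**Working it through.** **Inputs from the article.** Dropout about 15%; recruitment target 148; two equal arms, so 74 per arm.

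**The plan's own figures.** 128 × 1.15 = 147.2, which rounds up to the stated 148. Dividing instead gives 128 / 0.85 = 150.6, or 151. The two are close, and the difference plays no part here. Expected loss is 0.15 × 148 = 22.2, about 22 patients, or 0.15 × 74 = 11.1 per arm.

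**Assumed inputs.** The article gives no rate of negative effects. Let d be the share of an arm with no SEPS at any visit, p the rate among those seen and q the rate among those never seen. Setting d = 15% is an upper-end reading of the plan, because it treats every dropout as missing all of T1 to T3.

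**Formula.** True rate = (1 − d) × p + d × q. A complete-case summary returns p. Imputation from those seen also returns roughly p, if no other recorded variable predicts harm. The shortfall is therefore d × (q − p).

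**Results for d = 15%, p = 10%.**

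| q | True rate | Reported | Shortfall (points) |
|---|---|---|---|
| 10% | 8.5 + 1.5 = 10.0% | 10% | 0 |
| 20% | 8.5 + 3.0 = 11.5% | 10% | 1.5 |
| 25% | 8.5 + 3.75 = 12.25% | 10% | 2.25 |
| 50% | 8.5 + 7.5 = 16.0% | 10% | 6.0 |
| 100% | 8.5 + 15.0 = 23.5% | 10% | 13.5 |

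**Wider range.** For d from 10% to 20% and p from 5% to 20%, with q at or above p, the shortfall runs from 0 to 19 points. The maximum is at d = 20%, p = 5%, q = 100%: 0.20 × 95 = 19.

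**Between arms.** The error in the difference is the shortfall in one arm minus the shortfall in the other. If MBCT has q = 20% to 50% and OCD-EP has q = p = 10%, a true gap of 1.5 to 6 points would be reported as about 0. If both arms have the same d, p and q, the errors cancel.

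**What exit collection would recover.** Let r be the share of leavers who answer. The observed rate is ((1 − d)p + d·r·q) / ((1 − d) + d·r). In the 16.0% row:
- r = 0: 10.0%
- r = 50%: 0.1225 / 0.925 = 13.2%
- r = 80%: 0.145 / 0.97 = 14.9% (0.1495)
- r = 100%: 16.0%

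**The case against.** **Stopping sessions is not the same as having no data.** A reader might infer that anyone who leaves the group because of harm drops out of the harm data. The article does not support that. It defines non-completers by the absence of data at reassessment, adopts intent-to-treat, and nowhere says that patients who stop sessions are not reassessed. Such a patient can report at any of three later assessments. This stands, and it limits the point to patients never reassessed.

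**Imputing harm is not stated.** A reader might also infer that the SEPS will be filled in from attenders. The imputation sentence speaks of scores in general, among analyses of symptoms, response, remission and relapse. This stands too. The gap does not depend on imputation, because a complete-case summary has the same selection.

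**The article is condensed.** Adverse-event reporting and reasons for dropout may be in the full protocol or the case report file, which are not shown. Their absence here is not a finding. The point rests only on the stated timing of this questionnaire.

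**The size is assumed.** Every harm rate above is an assumption. A gap of 1.5 to 6 points is about 1 to 4 patients of 74, or roughly 0.3 to 1.1 standard errors of the difference (5 to 5.5 points). The analysis is exploratory, so this keeps the severity low. It does not remove the point, because reports that were never collected cannot be recovered in the analysis.

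**Conclusion.** The point holds in a limited form. As scheduled, this scale does not capture negative effects in patients who quit before T1 and are never reassessed. If their rate is higher than that of the patients seen, the reported rate in that arm is too low by d × (q − p). That is 0 to 13.5 points at 15% lost and an assumed 10% among those seen. The bias is zero if the rates are equal, and smaller if fewer than 15% miss every assessment or if recorded variables predict harm. The between-arm comparison is distorted only to the extent that the shortfalls differ between arms.

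The documents do not show that harm is understated, only that the schedule leaves it open. The primary Y-BOCS comparison is not touched. This is a cheap improvement of minor severity.

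**What to change.** In the Secondary outcomes section, add that the SEPS and the workgroup's items are also offered when a patient discontinues the group or withdraws, by post or telephone and only if the patient agrees. Record the reason for leaving if it is not already recorded.

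In the Statistical analyses section, add for all randomised patients, by arm:
- SEPS results;
- discontinuations with reasons, reported separately from the SEPS, because leaving a group for reasons such as inconvenience is not a negative effect;
- the number of patients with no SEPS at any time.

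If imputation is applied to negative effects at all, do not rely on a missing-at-random model for them.

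The cost is one existing questionnaire for about 22 patients and possibly one extra field. Some leavers will not reply, and exit reports follow a shorter exposure than T1 reports, so the two should be labelled as such.

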### Statistical analyses

Between-group comparisons at baseline will be performed using analyses of variance for the continuous variables and Fisher’s exact test for the categorical variables. Means and standard deviations will be calculated for descriptive purposes. The main analyses will be computed using analyses of covariance in view of statistical studies suggesting that controlling for the baseline score is superior to simple pre-post comparisons and usually leads to an increase in power. An advantage of this type of analysis over mixed models is that it accounts for baseline differences and regression to the mean (i.e. higher scores usually yield greater improvement). The rates of patients achieving response and/or remission and the relapse rates in both groups will be compared using Fisher’s exact test. The time to relapse will be estimated using Kaplan-Maier survival analyses. Survival curves will be compared using a log-rank-test. A cox-regression will be performed to analyze variables influencing the time to relapse. In order to prevent distortions, the intent-to-treat principle will be used. Multiple imputation will be adopted to estimate post-treatment and follow-up scores for non-completers (i.e. no data available at reassessment). The multiple imputation principle is considered superior to the last observation carried forward method (LOCF) [64]. When using the LOCF, follow-up data can be difficult to interpret [10].

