### The interventions

Both interventions will consist of eight sessions with a length of 120 minutes each, which will be held at weekly intervals in an outpatient setting at the University Medical Center of Freiburg and the University Medical Center Hamburg. Each treatment group will consist of eight to twelve participants.

MBCT is based on mindfulness training as developed by Jon Kabat-Zinn at the University Medical Center of Massachusetts, combined with psychoeducational elements from cognitive therapy. A detailed description of the original intervention can be found in Segal, Williams & Teasdale [15]. In the proposed trial, a modified version of the manual will be applied: The mindfulness elements are adopted from the original manual, and the cognitive elements are tailored to patients with OCD [35].

We intend to use an education program as an active control condition in order to control for unspecific effects of a group treatment. The program (OCD-EP) consists of a presentation and education about the etiology, mechanisms and maintaining factors of OC symptoms, metacognitive and neurobiological perspectives on OCD, information on existing pharmacotherapeutic and psychological treatment modalities and relapse prevention, group sharing and discussion. Behavior therapy techniques or mindfulness interventions are not part of the program.

The treatment sessions will be held by experienced behavioral therapists with longstanding experience in MBCT respective psychoeducation of OCD.

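### The main ANCOVA and the 128-patient calculation make no allowance for the 16 therapy groups; if outcomes correlate at all within groups, the primary test exceeds its 5% error rate

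*Protocol article*

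**What the plan says.** The Setting section fixes the number of therapy groups: "Overall, eight MBCT- and eight OCD-EP-groups will be conducted", four per arm at each site. The section on the interventions gives their size: "Each treatment group will consist of eight to twelve participants". Neither treatment is given individually.

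The Sample size section works from a standardised difference: "we assume a between-group effect size of *d* = 0.5 favoring MBCT". With power 0.8 and a 5% level it arrives at 128 patients, 64 per arm, for an F-test of the group-by-time interaction. The target then rises to 148, and dropout is the only reason given. No ICC or design effect appears.

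For the analysis, the Statistical analyses section says: "The main analyses will be computed using analyses of covariance in view of statistical studies suggesting that controlling for the baseline score is superior". It then sets ANCOVA above another class of model: "An advantage of this type of analysis over mixed models is that it accounts for baseline differences and regression to the mean". The only clustering the article addresses is by site, through stratification and uniform study conditions (Setting).

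**The concern.** Patients who attend the same eight sessions together may end up with outcomes more alike than those of patients in different groups of the same arm. If so, 64 patients in eight groups carry less information than 64 independent patients. An ANCOVA on individual patients does not see this. It then reports too small a standard error, too narrow a confidence interval and too small a p-value.

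The comparison at stake is the trial's main hypothesis, change in Y-BOCS from baseline to post-assessment. The follow-up comparisons are described as exploratory, so the confirmatory claim rests on this one test.

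The reason given for preferring ANCOVA to mixed models also fails. A mixed model for post-treatment Y-BOCS with baseline Y-BOCS as a covariate deals with baseline imbalance and regression to the mean just as ANCOVA does, and it can carry a therapy-group effect as well.

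**Working it through.** **Inputs from the protocol article.** d = 0.5, power 0.80, alpha 0.05, 64 analysed per arm (Sample size); 16 therapy groups (Setting). Analysed patients per group: m = 128/16 = 8. Enrolled patients per group: 148/16 = 9.25.

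**Inputs assumed.** The article gives neither an ICC nor a pre-post correlation r. ICC is taken as 0.01, 0.02, 0.05 and 0.10, and r is varied.

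**Step 1: reproduce the plan's figure.** For independent patients the noncentrality is 0.5 × √(64/2) = 2.83. On 126 df, the two-sided 5% t-test (the same as an F-test on 1 and 126 df) has power 0.8015. With 63 per arm it is 0.795. So 64 per arm, 128 in total, is exactly the independent-patients answer.

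**Step 2: standard error and type I error.** The design effect is DE = 1 + (m − 1) × ICC. The true standard error is √DE times the reported one. The true type I error of the nominal 5% test is about 2 × [1 − Φ(1.96/√DE)].

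| Assumed ICC | DE (m = 8) | True SE / reported SE | Type I error |
|---|---|---|---|
| 0 | 1.00 | 1.00 | 5.0% |
| 0.01 | 1.07 | 1.03 | 5.8% |
| 0.02 | 1.14 | 1.07 | 6.6% |
| 0.05 | 1.35 | 1.16 | 9.2% |
| 0.10 | 1.70 | 1.30 | 13.3% |

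The effect grows with group size. At the stated maximum of 12 and ICC 0.05, DE = 1 + 11 × 0.05 = 1.55 and the type I error is 11.5%.

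Baseline adjustment does not remove this excess, because what counts is the correlation that remains within groups after adjustment. A simulation of unadjusted patient-level ANCOVA (8 groups of 8 per arm, r = 0.5, 8,000 runs) gave 5.4%, 6.7%, 9.2% and 12.7% at ICC 0, 0.02, 0.05 and 0.10.

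**Step 3: power.** The noncentrality becomes 0.5 × √(64/(2 × DE)). The second column below uses the protocol's own basis, without baseline adjustment, on 126 df. The third column is for a test that respects the groups, with 16 − 2 = 14 df. The last column adds the planned baseline adjustment by replacing 0.5 with 0.5/√(1 − r²), which for an assumed r = 0.5 is 0.577.

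| Assumed ICC | No baseline adjustment, 126 df | No baseline adjustment, 14 df | Baseline-adjusted, r = 0.5, 14 df |
|---|---|---|---|
| 0.01 | 0.77 | 0.72 | 0.84 |
| 0.02 | 0.75 | 0.69 | 0.81 |
| 0.05 | 0.68 | 0.62 | 0.74 |
| 0.10 | 0.58 | 0.52 | 0.64 |

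The last column depends heavily on r. On 14 df, power runs from about 0.60 (r = 0.4, ICC 0.10) to about 0.93 (r = 0.7, ICC 0.02).

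**The case against.** **The size is conditional.** The article gives no ICC. At ICC 0 the ANCOVA standard error is correct, and at 0.01 the type I error is only 5.8%. Uniform training and rooms, with videotaped and supervised sessions checked for adherence (Setting), would tend to limit differences between groups. This stands as a limit on how much can be claimed. It does not show that the ICC is zero.

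**A reader might infer that the design does not deliver 0.80 power.** The documents do not support that. The 0.80 takes no credit for the baseline covariate in the planned analysis. At r = 0.5 and ICC 0.02, power that respects the groups is about 0.81; at r = 0.6 and ICC 0.05 it is also about 0.81. Whether there is a shortfall depends on two quantities that are not given.

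**A reader might take the Background's remark on unspecific group effects as the authors' own acknowledgement of clustering.** That remark explains why an active control was chosen. It concerns an average effect common to both arms, not correlation within a therapy group. Nor does the article say who leads which group, so a shared therapist cannot be cited as a known source of correlation. If one therapist led several groups, a therapy-group intercept alone would not capture it.

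**A condensed article may leave error structure to an analysis plan, and the mixed-model sentence is about handling baseline scores.** In context that is a fair reading: the sentence does not expressly reject an adjustment for therapy group, and cluster-robust inference is compatible with ANCOVA. But the article is not merely silent. It fixes an independent-patients sample size, names ANCOVA as the main analysis, and puts aside, for a mistaken reason, the class of model that would most naturally carry the group effect. Followed as written, the analysis ignores the groups.

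**Conclusion.** The analysis defect holds. Treatment in both arms is delivered in 16 therapy groups, and neither the sample size nor the stated main analysis takes account of them. For any positive ICC the primary test is anti-conservative: about 5.8% to 13.3% instead of 5% for assumed ICCs of 0.01 to 0.10 with 8 analysed patients per group, and more with larger groups.

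The power point is secondary and conditional. The 0.80 contains no allowance for clustering, which on the protocol's own basis would bring it to between 0.77 and 0.58 over the same ICCs. Baseline adjustment may recover part or all of that, so the documents do not establish that the trial is underpowered.

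**What to change.** 1. **Primary analysis.** Keep baseline Y-BOCS as a covariate and account for therapy group. Either add a random therapy-group intercept with Kenward-Roger or Satterthwaite degrees of freedom, or keep ANCOVA with cluster-robust standard errors and a small-sample correction. With only 16 groups the small-sample step is essential under either option.
2. **Rationale.** Delete the sentence that claims an advantage of ANCOVA over mixed models.
3. **Power.** Replace the single 0.80 with power for the chosen analysis over a stated range of ICC and pre-post correlation, with the assumptions shown.

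The cost is a change of wording, probably wider confidence intervals, and possibly a less favourable stated power. No extra patients or data are needed, provided that each patient's therapy group is on record.
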